## Abstract

**Introduction:**

Congenital anomalies are the fifth leading cause of death in children <5 years of age globally, contributing an estimated half a million deaths per year. Very limited literature exists from low and middle income countries (LMICs) where most of these deaths occur. The Global PaedSurg Research Collaboration aims to undertake the first multicentre, international, prospective cohort study of a selection of common congenital anomalies comparing management and outcomes between low, middle and high income countries (HICs) globally.

**Methods and analysis:**

The Global PaedSurg Research Collaboration consists of surgeons, paediatricians, anaesthetists and allied healthcare professionals involved in the surgical care of children globally. Collaborators will prospectively collect observational data on consecutive patients presenting for the first time, with one of seven common congenital anomalies (oesophageal atresia, congenital diaphragmatic hernia, intestinal atresia, gastroschisis, exomphalos, anorectal malformation and Hirschsprung's disease).

Patient recruitment will be for a minimum of 1 month from October 2018 to April 2019 with a 30-day post-primary intervention follow-up period. Anonymous data will be collected on patient demographics, clinical status, interventions and outcomes using REDCap. Collaborators will complete a survey regarding the resources and facilities for neonatal and paediatric surgery at their centre.

The primary outcome is all-cause in-hospital mortality. Secondary outcomes include the occurrence of post-operative complications. Chi-squared analysis will be used to compare mortality between LMICs and HICs. Multilevel, multivariate logistic regression analysis will be undertaken to identify patient-level and hospital-level factors affecting outcomes with adjustment for confounding factors.

**Ethics and dissemination:**

At the host centre, this study is classified as an audit not requiring ethical approval. All participating collaborators have gained local approval in accordance with their institutional ethical regulations. Collaborators will be encouraged to present the results locally, nationally and internationally. The results will be submitted for open access publication in a peer reviewed journal.

**Trial registration number:**

NCT03666767

Strengths and limitations of this studyThis will be the first large-series, geographically comprehensive, multicentre, international, prospective cohort study to define the management and outcomes of a selection of common congenital anomalies in low, middle and high income countries across the globe.The collaborative approach for this study allows a large series of high-quality data to be collected in a timely manner without overburdening high-volume, low-resource centres.The seven study conditions constitute a selection of the most common life-threatening congenital anomalies requiring emergency surgical care in the neonatal period (box 1).We recognise that some children may not reach a facility capable of providing acute paediatric surgical care and hence the results obtained may be an underestimation of true morbidity and mortality, especially in low and middle income countries.The number of variables being collected per patient has been limited to those known to have the greatest impact on outcomes to optimise the feasibility of the study; follow-up is limited to 30 days post-primary intervention.

## Introduction

In 2015, the Global Burden of Disease study concluded congenital anomalies (also known as congenital malformations, congenital abnormalities or birth defects) to be the fifth leading cause of death in children <5 years of age globally.^1^ This equates to approximately half a million deaths from congenital anomalies each year, 97% of which occur in low and middle income countries (LMICs). Indeed, this is likely to be an underestimation of the actual number of deaths due to underdiagnosis of neonates with congenital anomalies who die in the community and a lack of death certification in many LMICs.^2^ Not only is the mortality rate higher in LMICs, but the prevalence is also higher due to micronutrient deficiencies, infections and teratogens during pregnancy resulting in more cases and a lack of antenatal diagnosis prohibiting terminations.^3 4^ There is limited research and a lack of congenital anomaly registries in LMICs, and hence they have received very little global attention.^5^

The conditions forming the focus of this study (box 1) constitute a selection of the most common life-threatening congenital anomalies during the neonatal period, which involve the gastrointestinal tract. They each have an incidence of 1/2000 to 1/5000, they collectively form up to 40% of emergency neonatal surgery and associated mortality can be in excess of 50% in many LMICs.^6–9^ Disparities in outcomes globally can be stark; for example, the mortality from gastroschisis is 75%–100% in many LMICs compared with 4% or less in high income countries (HICs).^10–12^ Reasons for poor outcomes include a lack of antenatal diagnosis, delayed presentation, limited neonatal transport and in-hospital resources, a dearth of trained support personnel and a lack of intensive care and parenteral nutrition for neonates.^9 13 14^ In Uganda, it was calculated that only 3.5% of the need for neonatal surgery was met by the healthcare system.^8^

Box 1Congenital anomalies in the Global PaedSurg StudyOesophageal atresia ± tracheo-oesophageal fistulaCongenital diaphragmatic herniaIntestinal atresiaGastroschisisExomphalosAnorectal malformationHirschsprung’s disease

In 2010, the World Health Assembly passed a resolution recommending ‘prevention whenever possible, to implement screening programmes and to provide care and ongoing support to children with birth defects and their families’.^2^ Prevention is paramount; however, this is not yet possible for many congenital anomalies and hence a focus on improving postnatal care and outcomes is vital. The Sustainable Development Goal 3.2 aims to end preventable deaths of newborns and children under the age of 5 years by 2030.^6 15 16^ With one-third of infant deaths being attributed to congenital anomalies, clearly, this will not be achievable without an accelerated effort towards the provision of surgical care for children. It is estimated that two-thirds of deaths and disability from congenital anomalies can be avoided with the provision of neonatal and paediatric surgical care.^6^ Indeed, studies have demonstrated such provision can be highly cost-effective in terms of disability-adjusted life-years saved.^5^ Yet, neonatal and paediatric surgical care remains a low priority on the global health agenda.^5^

A shift is needed to focus on the provision of surgical care for children within National Health Plans and International Organisations and to elevate congenital anomalies on the global health agenda. This large-scale, geographically comprehensive, multicentre prospective cohort study aims to define the current management and outcomes of a selection of common congenital anomalies globally and identify factors affecting outcomes that can be modified to improve care. This is vital to aid advocacy and global health prioritisation and inform future interventional studies aimed at improving outcomes.

## Aim

To undertake the first large-scale, geographically comprehensive multicentre, prospective cohort study comparing the management and outcomes of a selection of common congenital anomalies in low, middle and high income countries across the globe.

## Objectives

To compare the mortality and post-intervention complications of a selection of common congenital anomalies involving the gastrointestinal tract in LMICs and HICs globally.To identify patient-level and hospital-level factors affecting outcomes that be modified to improve care.To establish a research collaboration consisting of children’s surgical care providers across the world to help enhance research capacity and to create a platform for ongoing collaborative research and intervention studies aimed at improving outcomes.To raise awareness and provide advocacy for neonatal and paediatric surgical care within global health prioritisation, planning, policy and funding.

## Methods and analysis

### Study design

This is an international, multicentre, prospective observational cohort study. The Global PaedSurg Research Collaboration consisting of children’s surgical care providers (collaborators) across the world was established from November 2017 to co-ordinate the study at an institutional level and facilitate data collection. Collaborators are free to choose one or more months between 1 October 2018 to 30 April 2019 (inclusive) to recruit consecutive patients to the study, with a 30-day post-primary intervention follow-up period. The primary intervention must occur within 30 days of presentation to be included in the study. Hence, the last date for primary data collection is 29 June 2019. Following this, there will be a period of data collection for the data validation process continuing until the end of August 2019.

### Sample selection

#### Collaborator and hospital inclusion criteria

All hospitals and healthcare professionals providing surgical care for neonates and children, presenting for the first time, with one or more of the study conditions can be included in the study. Collaborators should gain permission from the senior surgeon or physician who oversees the care of the children to be included in the study in order to participate. There can be up to three collaborators in a mini-team per month of data collection. One mini-team can collect data over one or more months or several mini-teams can collect data over a different month each. Each mini-team must contain at least one senior surgeon or physician to oversee the data collection process.

#### Patient inclusion and exclusion criteria

Any neonate, infant or child under the age of 16 years, presenting acutely for the first time, with one or more of the study conditions can be included in the study. Patients who have previously received surgery for their presenting condition or those representing with a complication of surgery are excluded. Patients presenting electively for surgery are excluded. Children who have received basic resuscitative care for their condition at a different healthcare facility and are then transferred to the study centre for their primary surgical intervention can be included. Children who only receive resuscitative treatment at the study centre and are then referred elsewhere for their primary surgical intervention cannot be included since the outcome of the surgical care will not be known and also to avoid the risk of duplicate patients in the study. Patients who receive conservative treatment as their primary intervention, palliative care or no care must be included within the study to accurately reflect the management and outcomes of all presenting cases.

If a patient presents with more than one of the study conditions, the details of each condition that they present acutely with can be included, but not a previously managed condition. For example, a newborn presenting with oesophageal atresia and anorectal malformation would have both conditions included. A patient presenting for the first time with Hirschsprung’s disease at several months of age who had a duodenal atresia repaired at birth would have the full details of the Hirschsprungs disease included, but the duodenal atresia would simply be noted as an associated anomaly.

### Outcome measures

The primary outcome is all-cause, in-hospital mortality.

For patient’s hospitalised for >30 days following primary intervention, a 30-day post-primary intervention mortality rate will be used. Those who do not receive a primary intervention, but remain alive and hospitalised at 30 days following primary admission, will have this time point used for recording their mortality status for the primary outcome. Primary outcome is defined in table 1.

**Table 1 T1:** Generic data points

Generic questions	Answers
During which month did the patient present to your hospital?	October, November, December, January, February, March, April. Please select the month that the patient presented to your hospital for the first time with this congenital anomaly. For example, if a baby was born with gastroschisis on the 29 September and presented to your hospital on 1 October you should select October.
Has consent been provided to include this patient in the study? If no, which condition did the patient present with?	Yes, No, Patient consent is not required for this study at my institution. Oesophageal atresia, Congenital diaphragmatic hernia, Intestinal atresia, Gastroschisis, Exomphalos, Omphalocele, Anorectal malformation, Hirschsprung's Disease. Please select all the conditions that the patient presented with. Do not select a condition which the patient has already received surgical treatment for previously.

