**Outcomes**	
Did the patient survive to discharge? If the patient was discharged prior, were they still alive at 30 days following primary intervention? If no, cause of death?	Yes, No. Select yes if the patient was still alive in your hospital 30 days after primary intervention or 30 days after presentation in patients who did not receive a primary intervention. Yes, No: not followed-up after discharge, Followed-up but not until 30 days post-primary intervention. This can include all reliable communication with the patient/patient’s family including in person, via telephone and other. Sepsis, aspiration pneumonia, respiratory failure, cardiac failure, malnutrition, electrolyte disturbance, haemorrhage, lack of intravenous access, hypoglycaemia, recurrent tracheo-oesophageal fistula, recurrent diaphragmatic hernia, anastomotic leak, ischaemic bowel, ruptured exomphalos sac, enterocolitis, other. If other, please specify.
Duration of hospital stay (days)	Please include the day of admission and the day of discharge in your calculation. For example, if a patient presented on 1 October and was discharged on the 5 October, their duration of hospital stay would be 5 days. If the patient died, please record the number of days from admission to death. Only include the duration of the primary admission, not subsequent admissions if the patient re-presented.
Did the patient have a surgical site infection?	Yes, No, Not applicable: no surgical wound. This is defined as one or more of the following within 30 days of surgery: (1) purulent drainage from the superficial or deep (fascia or muscle) incision, but not within the organ/space component of the surgical site OR (2) at least two of: pain or tenderness, localised swelling, redness, heat, fever, AND the incision is opened deliberately to manage infection, spontaneously dehisces or the clinician diagnoses an SSI (negative culture swab excludes this criterion) OR (3) there is an abscess within the wound (clinically or radiologically detected).
Did the patient have a full thickness wound dehiscence?	Yes, No, Not applicable — no surgical wound. This is defined as all layers of the wound opening within 30 days of surgery.

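### The window in which a primary-outcome death is counted runs from 30 to 60 days depending on whether and when the infant was treated, so any time-to-intervention association with mortality is partly built in

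*Protocol article*

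**What the plan says.** Under Outcome measures the outcome is named without a time limit: "The primary outcome is all-cause, in-hospital mortality". Two rules then close it for patients who stay in hospital.

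- **Treated, in hospital more than 30 days after intervention:** "a 30-day post-primary intervention mortality rate will be used".
- **Untreated:** the rule covers "Those who do not receive a primary intervention, but remain alive and hospitalised at 30 days following primary admission". Their status on that day is taken as the primary outcome.

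Table 1 (Outcomes) carries both rules into the survival question on the data form: "Select yes if the patient was still alive in your hospital 30 days after primary intervention or 30 days after presentation", the second limb being for patients without a primary intervention.

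Study design sets the latest intervention, "The primary intervention must occur within 30 days of presentation to be included in the study", and the recruitment period, "between 1 October 2018 to 30 April 2019 (inclusive) to recruit consecutive patients to the study". It gives 29 June 2019 as the last date for primary data.

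The inclusion criteria require patients given palliative care or no care to be included. Data analysis compares mortality between LMICs and HICs for each condition by a chi-squared or exact test. It then screens covariates against mortality by logistic regression before fitting multilevel models. Table 1 also records hours from arrival to primary intervention, entered as 0 where there was none. For deaths it says: "If the patient died, please record the number of days from admission to death".

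**The concern.** A binary outcome compared between groups should give each patient the same opportunity for the event to be recorded. Here patients are followed from presentation, but the closing date moves with the intervention date. For infants who stay in hospital, a later intervention lengthens the period in which a death counts.

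Two analyses could be touched. The LMIC-HIC test pools treated and untreated patients without adjustment, so unequal delay or non-treatment would mean unequal counting periods. The second is more direct. The study looks for modifiable factors that affect outcome, and time to intervention is a collected variable. If it is related to mortality, part of the association will come from the outcome definition, because each day of delay adds a day of counting. The planned logistic models, as described, make no allowance for length of observation.

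**Working it through.** **1. Reproduce the plan's own date.** Last recruitment is 30 April 2019. Adding 30 days to the latest intervention gives 30 May, and adding 30 days of follow-up gives 29 June 2019. This matches the stated date, so the longest window is 60 days from presentation.

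**2. Closing day.** Take presentation, arrival and admission as the same day 0. For a patient still in hospital, C = t + 30 if treated on day t (0 to 30), and C = 30 if untreated.

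| Treated on day | Closing day | In-hospital death on day 35 |
|---|---|---|
| Untreated | 30 | Scored as survival |
| 0 | 30 | Scored as survival |
| 4 | 34 | Scored as survival |
| 5 | 35 | On the boundary |
| 6 | 36 | Scored as death |
| 20 | 50 | Scored as death |
| 30 | 60 | Scored as death |

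**3. Link to the covariate.** Because untreated patients are entered as 0 hours, the longest possible window equals 30 days + (recorded hours to intervention ÷ 24) for treated and untreated alike. Adjusting for that variable cannot separate an effect of delay from longer counting.

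**4. Illustrative size.** The document gives no death rate after day 30 and no distribution of delay, so these inputs are assumptions. Take a daily death risk r of 0.2% to 0.5% in infants who stay in hospital throughout the extra d days. Added recorded mortality among them is 1 − (1 − r)^d.

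- d = 10: 1 − 0.998^10 = 2.0%; 1 − 0.995^10 = 4.9%.
- d = 30: 1 − 0.998^30 = 5.8%; 1 − 0.995^30 = 14.0%.

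If such infants are 10% of one group and absent from the other, the shift is 0.10 × 2.0% = 0.2 points up to 0.10 × 14.0% = 1.4 points.

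A wider set of assumptions takes a share f of 10% to 50% and a daily hazard h of 0.001 to 0.01, with shift f × (1 − e^(−hd)). It gives 0.1 to 4.8 points for 10 extra days and 0.3 to 13.0 points for 30. The top corner needs half of one group to be treated on day 30 and kept in hospital at a 1% daily hazard, with no such patients in the other group.

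**5. Against the expected gaps.** LMIC minus HIC mortality from Table 2, in percentage points:

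| Condition | Gap |
|---|---|
| Oesophageal atresia | 43.7 − 2.7 = 41.0 |
| Diaphragmatic hernia | 47.4 − 20.4 = 27.0 |
| Intestinal atresia | 41.0 − 2.9 = 38.1 |
| Gastroschisis | 56.6 − 3.7 = 52.9 |
| Exomphalos | 30.1 − 12.7 = 17.4 |
| Anorectal malformation | 18.1 − 3.0 = 15.1 |
| Hirschsprung's disease | 17.6 − 2.3 = 15.3 |

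A shift of 1.4 points is 1.4 ÷ 15.1 = 9% of the smallest gap and 1.4 ÷ 52.9 = 3% of the largest.

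**6. Can a common clock be derived?** Every patient is followed in hospital to day 30 from presentation, or to earlier discharge or death, because t + 30 is never below 30. Days from admission to death are recorded, and the secondary outcomes section keeps that item for untreated patients. In-hospital death by day 30 therefore needs no new data.

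**The case against.** The text is consistent with itself: Outcome measures, Table 1 and the end date all agree, so this is a disclosed design choice and not a contradiction. Thirty-day post-intervention mortality is a natural measure for surgical care. A clock from presentation has a fault of its own: an infant operated on at day 28 would have 2 days of post-operative observation, and one operated on at day 1 would have 29. That could make late surgery look safer. Nor does a common clock equalise everything, since an in-hospital outcome still ends at discharge. These points stand, and they are why replacing the primary outcome is not the right remedy.

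A reader might infer that part of the LMIC-HIC difference is an artefact of unequal counting. The document does not support that. Longer delay in LMICs would lengthen the window, but more untreated infants would shorten it, and no figures for either are given by income group. The delayed presentation mentioned in the Introduction precedes arrival and does not move this clock. Long in-hospital delays may also be uncommon: patients present acutely, elective cases are excluded, and primary intervention includes measures such as silo application, topical sac treatment and irrigation.

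A reader might also infer that untreated infants are singled out for the shortest window. An infant treated on day 0 has the same closing day.

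Finally, Data analysis does not name time from arrival to intervention as a covariate. It is collected and is an obvious candidate, but the exposure depends on its being analysed.

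**Conclusion.** The point holds in a limited form. For patients still in hospital, the counting period depends on receipt and timing of care and runs from 30 to 60 days. This follows from the protocol's own rules and dates.

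Only infants still admitted after day 30 are affected. The size and direction of any effect on the LMIC-HIC comparison cannot be computed from the document. Under the working assumptions it is 0.2 to 1.4 points, too small to overturn expected gaps of about 15 to 53 points. Calling it small rests on late-treated, long-stay infants being a minority, because the extreme corner of 13.0 points would not be small.

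The consequence that does not depend on those assumptions concerns time to intervention. Whenever any infants die in hospital after day 30, part of its association with the stated outcome comes from the definition, and adjustment cannot remove it.

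**What to change.** - Derive in-hospital death by day 30 from presentation for every patient, treated or not, from the recorded days from admission to death. State whether the admission day is day 0 or day 1, since the length-of-stay item counts both end days.
- Report the LMIC-HIC comparison and the regression models on this common clock alongside the stated primary outcome.
- Use the common clock for any inference about time to intervention or receipt of it.
- Keep 30-day post-intervention mortality as the secondary outcome it already is.

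The cost is one derived variable and a repeat of the analyses, with no new data collection. The report should state the downside: on the common clock, late-operated patients have shorter post-operative observation, and their deaths after day 30 appear only in the stated primary outcome and in the secondary outcome.
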